## Abstract

**Background:**

Sepsis is the leading cause of intensive care unit (ICU) admission and ICU death. In recognition of the burden of sepsis, the Surviving Sepsis Campaign (SSC) and the Institute for Healthcare Improvement developed sepsis “bundles” (goals to accomplish over a specific time period) to facilitate SSC guideline implementation in clinical practice. Using the SSC 3-h bundle as a base, the Centers for Medicare and Medicaid Services developed a 3-h sepsis bundle that has become the national standard for early management of sepsis. Emerging observational data, from an analysis conducted for the AIMS grant application, suggest there may be additional mortality benefit from even earlier implementation of the 3-h bundle, i.e., the 1-h bundle.

**Method:**

The primary aims of this randomized controlled trial are to: (1) examine the effect on clinical outcomes of Emergency Department initiation of the elements of the 3-h bundle within the traditional 3 h versus initiating within 1 h of sepsis recognition and (2) examine the extent to which a rigorous implementation strategy will improve implementation and compliance with both the 1-h bundle and the 3-h bundle. This study will be entirely conducted in the Emergency Department at 18 sites. A secondary aim is to identify clinical sepsis phenotypes and their impact on treatment outcomes.

**Discussion:**

This cluster-randomized trial, employing implementation science methodology, is timely and important to the field. The hybrid effectiveness-implementation design is likely to have an impact on clinical practice in sepsis management by providing a rigorous evaluation of the 1- and 3-h bundles.

**Trial registration:**

ClinicalTrials.gov NCT05491941. Registered on August 8, 2022.

**Supplementary Information:**

The online version contains supplementary material available at 10.1186/s13063-023-07644-y.

## Background

Sepsis is the leading cause of admission to intensive care units (ICUs), the leading cause of death in ICUs, and the most common cause of hospital readmissions [1–6]. Sepsis is also the most expensive condition treated in the USA [7]. The Surviving Sepsis Campaign (SSC) was formed in 2002 to reduce sepsis mortality. SSC developed evidence-based guidelines in 2004, and updated guidelines in 2008, 2013, 2017, and 2021 [8–11]. Since simply publishing guidelines seldom leads to changes in clinical behavior [12], the SSC in partnership with the Institute for Healthcare Improvement [13] developed sepsis “bundles” to change clinical practice. A bundle aggregates evidence-based practices into a discrete management approach. Initial 6- and 24-h SSC bundles were revised to 3- and 6-h bundles, and subsequently to the 1-h bundle [14].

Since the advent of sepsis bundles, multiple observational studies have demonstrated an association between implementation of sepsis bundles and improved survival [15–35]. Adoption has been widespread [16, 36–38]. Higher bundle compliance is associated with lower mortality [39–41]. Based on these data and since sepsis is a “medical emergency” [7], all 3-h bundle elements were included in the 1-h bundle in recognition that earlier management might improve survival [14]. The 1-h bundle was named to differentiate the importance of initiating all the elements within that hour as opposed to completion. Although some hospitals have adopted the 1-h bundle, widespread adoption has not occurred.

In 2015 the Centers for Medicare and Medicaid Services (CMS) introduced “The Early Management Bundle: Severe Sepsis/Septic Shock” (SEP-1), which requires hospitals to report compliance with certain clinical processes related to sepsis care. SEP-1 focuses on timely recognition and early intervention. Despite the CMS reporting requirement, hospital compliance remains moderate at 60% [42].

Although bundle compliance would appear essential to improve sepsis outcomes, implementation science approaches to improve bundle compliance have not been evaluated. In particular, there is no widely accepted implementation strategy (i.e., a method to enhance adoption of identified practices) [43] to promote compliance with sepsis bundles. Application of rigorous implementation science techniques, identifying both barriers and facilitators, may improve bundle compliance [44].

This pragmatic, cluster-randomized hybrid type 2 effectiveness-implementation study will compare the effectiveness of the 1-h bundle to the 3-h bundle. The implementation strategy will be guided by the EPIS (Exploration, Preparation, Implementation, Sustainment) Framework [45], a commonly used approach that delineates phases of implementation and associated constructs. This study will explicitly test rigorous implementation strategies and incorporate formative, process, and summative evaluations throughout. In addition, sepsis phenotypes will be identified to probe how sepsis bundles may interact with a specific clinical presentation.

## Methods

### Study design

This study is a pragmatic, cluster-randomized trial of 18 hospitals (9 in each arm) comparing the 1- and 3-h bundles in patients presenting to emergency departments (ED) with sepsis. We will use a hybrid type 2 effectiveness-implementation design [46] to evaluate (1) effectiveness outcomes, including mortality and respiratory failure, and (2) implementation outcomes, including compliance (Fig. 1). The multi-faceted implementation strategy will apply to both trial arms. Application of the Pragmatic Explanatory Continuum Indicator Summary [47–50] (PRECIS) tool identifies this trial as pragmatic (vs. explanatory) [51]. A cluster-randomized trial is appropriate for analyzing the comparative effectiveness of the 1-h bundle versus the 3-h bundle because of the impossibility of randomizing patients to a particular approach and the importance of implementation of bundles at the hospital level. This protocol adheres to the Standard Protocol Items: Recommendations for Interventional Trials (SPIRIT) guidelines [52]. Figure 2 provides a summary of the enrollment schedule, interventions, and assessments using the SPIRIT flow diagram.

**Fig. 1 Fig1:**
[figure not shown]
Study timeline

**Fig. 2 Fig2:**
[figure not shown]
SPIRIT checklist: Schedule of enrollment, interventions and assessment

### Study objectives

The study aims are as follows: (*Aim 1*) Examine comparative effectiveness of the 1-h versus 3-h sepsis bundle on the primary outcome of hospital mortality and secondary outcomes of length of stay, ventilator-free days at 28 days, and rate of acute respiratory failure requiring mechanical ventilation. *Hypothesis:* The 1-h bundle will have lower hospital mortality. (*Aim 2*): Conduct a mixed methods evaluation of a multi-faceted implementation strategy to enhance compliance with the 1 and the 3-h bundles. *Hypothesis*: 1 and 3-h bundle implementation compliance will be similar as assessed by (a) the electronic health record (EHR), (b) surveys of key informants regarding implementation climate, organizational readiness for change, and implementation leadership, (c) recordings of learning collaborative meetings, and (d) interviews with participants. (*Aim 3*): Determine if clinical sepsis phenotypes determined by characteristics measured at presentation modify the treatment effect of the 1 or 3-h bundle. *Hypothesis:* Routine clinical information available at ED presentation will identify phenotypes more likely to benefit from the 1 or 3-h bundle.

### Study setting

We will conduct this study at 18 diverse acute care hospitals in the USA. Hospital selection was based upon responses of ED leaders to a baseline survey to ensure a diverse and representative sample of hospitals. Considerations included hospital size, teaching status, and known improvement strategies. Discovery, the Society of Critical Care Medicine’s (SCCM) critical care research network, will serve as clinical and data coordinating center for the study. Sites were recruited from Discovery and via polling emergency medicine members of SCCM as to suitability of their hospital as a site. Both academic and community hospitals are included to support the pragmatic nature of the study and ensure generalizability. To account for baseline implementation efforts, prior to randomization, sites that reported less than 30% or more than 70% compliance with SEP-1 were not included for study participation. Patient inclusion criteria include suspected severe sepsis and/or septic shock in the ED with 2 out of 4 Systematic Inflammatory Response Syndrome (SIRS) criteria, evidence of organ dysfunction, and suspected infection—consistent with the criteria established for SEP-1 by CMS. Time zero (the beginning of measuring compliance with the 3-h bundle) is defined in the same manner as described by CMS—all three criteria have to be met within 6 h in order for the definition of time zero to be met. Patients will be excluded if, within 24 h of admission, they are made do-not-resuscitate/do-not-intubate, comfort measures only, or considered not eligible to full aggressive care because of patient or family wishes. For consistency, only hospitals utilizing Epic as their EHR were included. In addition, the decision was made by the investigators that if patients do not present with hypotension, but develop hypotension after the criteria for time zero are met, then no fluids will be given. This does not mean that no fluids will be given to a patient, but rather that, for the purposes of the AIMS study compliance with fluids will not be measured.

### Randomization

Hospitals will be randomized to one of two arms (1- or 3-h bundle) in a 1:1 ratio. Randomization will be accomplished using randomly permuted blocks of variable size and controlling for academic or community status. Hospital physician and nurse dyads will be told which condition they were randomized to during in-person meetings at SCCM immediately prior to the Implementation Phase; separate meetings will take place for each study arm. Each arm will undergo a 30-month structured, collaborative implementation approach to operationalize compliance with their bundle assignment. The elements of both bundles are identical—only the timing is different (see Table 1). In this cluster-randomized clinical trial, the hospital is the unit of randomization. Hospitals will be informed as to their randomized arm after the baseline collection period. The randomization will be done by the study statistician and held only in the statistician’s computer until the reveal meeting at the end of the baseline period. Due to the pragmatic, open-label design of this trial and its objective measurement of study outcomes, the study staff, investigators, sites, and biostatisticians will not be masked to treatment condition once randomization occurs. Patients will receive standard of care for sepsis and their data will be collected retrospectively by the hospital each month.

**Table 1 Tab1:** 1- and 3-h bundle elements: quality and outcome indicator definitions and specifications

	**Definition of bundle element (quality indicator) or outcome measure obtained from the EHR by site staff**	**Both study arms**
**Bundle element**		
1	Indicate if patient with sepsis or septic shock had an initial lactate drawn	Initiated or completed within 1 or 3 h following the time of presentation in the ED
2	Indicate if patient had blood cultures collected prior to broad-spectrum antibiotics for sepsis and/or septic shock	Initiated or completed within 1 or 3 h following the time of presentation in the ED
3	Time in minutes to receipt of broad-spectrum antibiotics for sepsis and/or septic shock following the time of presentation in the ED	Initiated or completed within 1 or 3 h following the time of presentation in the ED
4	Indicate if patient had 30 ml/kg IVF bolus initiated if hypotensive or with a lactate ≥ 4 mmol/L on presentation in the ED	Initiated or completed within 1 or 3 h following the time of presentation in the ED or n/a
5	Indicate if patient with persistent hypotension received vasopressors to achieve mean arterial pressure > 65 mmHg	Initiated or completed within 1 or 3 h following the time of presentation in the or n/a
6	The percent of cases of sepsis and/or septic shock that completed all elements of the bundle	Initiated or completed within 1 or 3 h following the time of presentation in the ED
7	The percent of all patients that completed all elements of the bundle	Initiated or completed within 1 or 3 h following the time of presentation in the ED
**Outcome measures**		
A	Hospital mortality for patients with sepsis and/or septic shock (primary outcome)	Yes vs. no
B	Hospital days for patients with sepsis and/or septic shock	Count
C	Indicate if mechanical ventilation present during admission for patients with sepsis and/or septic shock	Yes vs. no
D	Days alive and free from mechanical ventilation	Count

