##### Secondary outcomes

Four secondary outcomes will be investigated: respiratory failure requiring mechanical ventilation, the number of ventilator-free days, and hospital and ICU length of stay. The same statistical approach described in the primary analysis will be used here; however, the analysis for the count of ventilator-free days will be based on random-effects negative binomial regression or a zero inflated negative binomial regression, depending on the distribution of the count of ventilator-free days. Similar to hospital mortality, the requirement for mechanical ventilation will be based on random-effects logistic regression. Hospital length of stay analysis will be based on a random-effects linear regression. However, prior to the analysis, length of stay will be normalized using the natural logarithm since this variable is not normally distributed. After running the random-effects linear regression, the results will be back transformed to the original units producing the ratio of the geometric mean length of stay for patients in one arm compared to the other arm.

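### Table 1 scores any ventilation during the admission, which is broader than the respiratory-failure outcome the article names and dilutes its effect by an unknown, possibly small, amount

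*Protocol article*

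**What the plan says.** The outcome appears in three places in the protocol article, and the wording differs.

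- **Study objectives, Aim 1:** "rate of acute respiratory failure requiring mechanical ventilation".
- **Analysis plan, Secondary outcomes:** "respiratory failure requiring mechanical ventilation", without the word acute. The model is then described this way: "the requirement for mechanical ventilation will be based on random-effects logistic regression", following the approach of the primary analysis (arm, period and their interaction, with hospital as random term).
- **Table 1, Outcome measures, item C:** "Indicate if mechanical ventilation present during admission for patients with sepsis and/or septic shock", scored yes or no. By its title and column heading, Table 1 holds the definitions and specifications of outcome indicators that site staff take from the electronic health record.

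Two other sections could have narrowed item C but do not. The patient exclusion in Study setting concerns limits to care set during the first 24 hours: "they are made do-not-resuscitate/do-not-intubate, comfort measures only, or considered not eligible to full aggressive care because of patient or family wishes". It says nothing about ventilation already under way. Among the listed sensitivity analyses, the one on care received after presentation gives fluids and antibiotics before arrival as its examples, not ventilation.

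**The concern.** Item C drops both qualifiers in the named outcome: that the failure is acute, and that respiratory failure is the reason for ventilation. Read as written, a patient on long-term ventilation scores yes, and so does one who arrives already intubated. Whether the bundle is started within 1 h or 3 h cannot change either result.

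Such events enter both arms. They pull the odds ratio towards 1 and reduce the chance of seeing a real effect on ventilation. Interpretation is affected too. The section on anticipated findings plans a conclusion about respiratory failure and calls a negative result particularly important. A variable that records ventilation of any onset and for any reason does not directly support the first, and it leans towards the second.

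**Working it through.** **Plan's own figure.** There is none to reproduce. The article states no rate, effect size or power for ventilation, so every input below is an assumption.

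**Inputs (assumed).**
- p = share already ventilated, the same in both arms and unaffected by the bundle: 1–8%.
- q = rate of new ventilation among the rest, 3-h arm, post-intervention: 12–30%.
- Relative reduction in new ventilation in the 1-h arm: 15% (risk ratio 0.85).
- Equal baseline rates in the two arms, so that the arm-by-period odds ratio equals the post-intervention odds ratio. Hospital clustering is ignored; this is a calculation of dilution, not of the trial's power.

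**Formulae.**
- Recorded rate, 3-h arm: a = p + (1 − p)q
- Recorded rate, 1-h arm: b = p + (1 − p)(0.85q)
- Recorded risk difference: a − b = (1 − p)(0.15q), so its relative shrinkage is exactly p.
- Recorded odds ratio: [b/(1 − b)] / [a/(1 − a)]
- Loss = 1 − ln(recorded odds ratio) / ln(odds ratio for new ventilation)

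**Upper end, p = 8%, q = 12%.**
- a = 0.08 + 0.92 × 0.12 = 0.1904; b = 0.08 + 0.92 × 0.102 = 0.1738.
- New ventilation: (0.102/0.898) / (0.12/0.88) = 0.833, log −0.183.
- Recorded: (0.1738/0.8262) / (0.1904/0.8096) = 0.895, log −0.111.
- Loss = 1 − 0.111/0.183 = 39%. The risk difference falls from 1.80 to 1.66 percentage points (8%).

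**Lower end, p = 1%, q = 30%.**
- a = 0.01 + 0.99 × 0.30 = 0.3070; b = 0.01 + 0.99 × 0.255 = 0.2625.
- New ventilation: odds ratio 0.799, log −0.225. Recorded: 0.803, log −0.219.
- Loss about 3%. The risk difference falls from 4.50 to 4.46 percentage points (1%).

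| p | q | Odds ratio, new ventilation | Odds ratio, as recorded | Log odds ratio lost | Risk difference lost |
|---|---|---|---|---|---|
| 1% | 12% | 0.833 | 0.844 | 7% | 1% |
| 3% | 15% | 0.828 | 0.853 | 16% | 3% |
| 5% | 20% | 0.819 | 0.849 | 18% | 5% |
| 8% | 12% | 0.833 | 0.895 | 39% | 8% |
| 1% | 30% | 0.799 | 0.803 | 3% | 1% |
| 8% | 30% | 0.799 | 0.830 | 17% | 8% |

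The direction holds for any p above zero, and at p = 0 nothing is lost. The size depends on p relative to q. If the bundle has no effect on new ventilation, a and b are equal, so a share that is the same in both arms and stable over time creates no false arm-by-period effect.

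**The case against.** The strongest reply is that item C is one line in a condensed article. The Data Subcommittee builds the report form and the data-entry training, and these may already hold start times and rules for long-term ventilation. That is fair as to what abstractors will do in practice, which the article does not show. It does not remove the mismatch: the article prints a specification, and that specification is wider than the outcome it names.

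Second, any ventilation, yes or no, is objective. The Randomization section relies on objective outcomes to justify open-label conduct. Asking unmasked staff to judge whether respiratory failure was the cause would weaken that. Excluding patients ventilated before time zero could also select the denominator differently by arm. Time zero depends on when the criteria are met ("all three criteria have to be met within 6 h in order for the definition of time zero to be met"), and sites develop automated sepsis alerts during the implementation phase. Both points stand and shape the remedy.

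Three stronger readings go beyond the text:
- A reader might infer that Aim 1 names new respiratory failure after time zero. It says acute. A patient intubated for septic respiratory failure shortly before time zero fits that wording.
- A reader might infer that the entry criterion and the endpoint are the same event, because entry requires "evidence of organ dysfunction". The article does not list which dysfunctions qualify, so this cannot be shown.
- A reader might turn the lost log odds ratio into a required increase in patients. That treats patients as independent, whereas this trial has 18 fixed hospitals and a random hospital term.

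**Conclusion.** The point holds as a mismatch of definition with a known direction. Table 1 item C is broader than the outcome in Study objectives and Secondary outcomes, and no exclusion or sensitivity analysis shown narrows it. Patients already ventilated on arrival, or on long-term ventilation, count as events that bundle timing cannot prevent, which attenuates the effect.

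The size is not derivable from the document and may be small: roughly 3–39% of the log odds ratio and 1–8% of the risk difference, under the assumed ranges and an assumed 15% relative reduction. The consequence is confined to one secondary outcome. A reader might infer that the trial's main result or its type I error is at risk. It is not: hospital mortality does not use this variable, and a share that is equal between arms and stable over time produces dilution only.

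**What to change.** Reconcile Study objectives, Table 1 item C and Secondary outcomes on one definition.

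- **Event:** mechanical ventilation started after ED arrival, stating which forms of ventilation count (invasive only, or others by name), taken from the start time in the electronic record.
- **Denominator:** leave out patients already ventilated on ED arrival or on long-term ventilation, for this endpoint only.
- **Anchor:** use ED arrival or triage time, not time zero, and ask for no judgement of cause by unmasked staff. Some events that the bundle cannot prevent will remain, such as ventilation begun between arrival and time zero or for a procedure. That is the price of an objective rule.
- **Periods:** apply the same rule to the baseline and outcome periods. Data are abstracted retrospectively, so baseline start times should be recoverable.
- **Sensitivity analysis:** keep any ventilation during the admission, as now recorded.
- **Conclusion:** under anticipated findings, limit the claim to ventilation as measured rather than respiratory failure.

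The cost is one extra time stamp per ventilated patient and a slightly smaller denominator for one secondary outcome. Item D, the ventilator-free-days count, already needs ventilation duration from the same record, so the added work should be modest.

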### Implementation strategies

The implementation package consists of six strategies (see Table 2) from the Expert Recommendations for Implementing Change (ERIC) [53] strategy taxonomy and carried out by the study team according to the Exploration, Preparation, Implementation, Sustainment (EPIS) [54] phase. The only difference in the implementation package for the two arms is training specific to implement the bundle assignment.

**Table 2 Tab2:** Overview of implementation strategies by study phase

Implementation strategy	EPIS phase
Change the record system	Exploration (6 months)
Implementation formative evaluation: Assess Readiness and barriers and facilitators	Exploration (6 months)
Identity and prepare champions	Adoption/preparation (6 months)
Create a learning collaborative	Adoption/preparation (6 months)
Conduct ongoing trainings	Implementation (30 months)
Develop and implement tools	Implementation (30 months)
Audit and feedback	Implementation (30 months)
Implementation process evaluation	Implementation (15 months)
Implementation summative evaluation	Sustainment (6 months)
Distribute educational materials	Sustainment (6 months)

#### ***Exploration phase (6 months) (***Fig. 1***)***

##### Assess for readiness, organizational culture, and barriers and facilitators

Prior to implementation, sites will participate in formative evaluations [55], which will involve: First, *surveys with ED leadership* (physician and nurse dyads) to explore leadership and team attitudes and engagement, assess their needs related to sepsis bundle adoption, explore anticipated barriers to implementation, and identify potential facilitators of change. We will use several scales during the exploration phase, and then again at the conclusion of the Implementation phase: (a) Implementation Leadership Scale (ILS) [56]; (b) Evidence-Based Practices Attitudes Scale (EBPAS-15) [57]; (c) Organizational Readiness for Implementing Change (ORIC); and (d) Implementation Climate Scale (ICS) [58]. Secondly, *semi-structured interviews with key ED informants* will occur during the formative, process, and summative evaluation phases [59]. Leaders, physicians, nurses, and other hospital staff will be asked about their openness/resistance to change generally and to the use of sepsis bundles, beliefs about the evidence supporting sepsis bundles, perceptions of the utility of the bundles, fiscal obstacles (or facilitators), and beliefs about the importance of timely treatment.

